#### Storage of Study Drugs

The investigational product and placebo will be stored at room temperature (20°C‐25 °C) in accordance with local institutional practices. Temperature monitoring will be performed when facilities are available; otherwise, the drugs will be stored at ambient room temperature under appropriate conditions to maintain stability.

### Data Collection and Management

Data will be collected by trained staff at each center using standardized case report form (CRF) booklets and entered into a password-protected REDCap (Vanderbilt University) electronic database. As each participant is given a unique enrollment ID, the data will be collected in a deidentified manner. Data will include demographics, medical history, comorbidities, details of the hanging event, and findings from a complete physical examination. Baseline investigations will comprise a complete hemogram, renal and liver function tests, serum electrolytes, random blood sugar, chest X-ray, ECG, and arterial blood gas analysis with PaO₂ and PaO_2_/FiO_2_ (PF) ratio. NCCT of the head and cervical spine will be performed when clinically indicated to evaluate for cerebral edema or cervical spine injury.

During the first 5 days of hospitalization, patients will undergo daily monitoring of physiological status, neurological function, organ dysfunction, and treatment variables. Neurological status will be assessed using the GCS at admission, every 6 hours on day 1, and every 24 hours thereafter, with adjustments for sedation. Hemodynamic parameters, including heart rate, mean arterial pressure, and the requirement for vasoactive agents, will be recorded, along with respiratory parameters such as respiratory rate, PF ratio, and ventilatory status. The need for organ support, including mechanical ventilation, inotropes, and sedatives, as well as details of antibiotic therapy, will be documented. Sequential Organ Failure Assessment (SOFA) scores will be calculated using platelet count, serum creatinine, bilirubin, mean arterial pressure or vasopressor requirement, PF ratio, and GCS at predefined time points.

Laboratory monitoring will be conducted to assess disease progression and potential steroid-related adverse effects. On days 2 and 3, a complete hemogram, blood glucose levels, and serum potassium will be measured to screen for complications such as infection, hyperglycemia, and hypokalemia. If steroid therapy is continued beyond day 3, similar laboratory monitoring will be repeated on days 4 and 5. SOFA scores will be recalculated on days 3 and 5. This monitoring schedule is shown in Table 2.

**Table 2. T2:** Monitoring schedule (days 1‐5).

Domain	What is measured	Day 1	Day 2	Day 3	Day 4	Day 5

### Assessment at Discharge

The outcome assessment will include the GOS at discharge (shown in Table 3) [24]. We will also assess the duration of study medication, whether full sensorium is achieved during hospitalization, and the time taken to achieve full sensorium (defined as a GCS score of 15 maintained for more than 24 h). Additional outcomes will include the duration of hospital stay and intensive care unit stay, the need for ventilatory support, including its duration and type, and the requirement for vasoactive support and its duration, if applicable. All AEs, as defined in the study protocol, will be documented. For participants who do not complete the study, the reasons for noncompletion will be recorded in detail.

**Table 3. T3:** Glasgow Outcome Scale (GOS) for neurological outcome [24].

GOS score	Rating	Description	Outcome category
1	Death	Death	Poor
2	Persistent vegetative state	Patient unresponsive and speechless for weeks or months	Poor
3	Severe disability	Dependent for daily support	Poor
4	Moderate disability	Disabled but independent	Good
5	Good recovery	Resumption of normal life with minor neurological and psychological deficits	Good

### Outcome Assessment on Day 28

The patient will be called for a follow-up on day 28 to assess GOS. The outcome will be assessed by the study staff who are blinded to the treatment allocation. If the patient cannot attend in person, GOS will be ascertained by telephone or video call. A standardized, structured interview process will be followed during the outcome assessment. Participants who die before day 28 will be assigned a GOS of 1 and will be included in the primary outcome analysis.

### Definition of the End of Study

The end of the study is defined as the time when the last participant has either completed the 28-day follow-up or discontinued the study early.

### Withdrawal Criteria

Each participant is free to discontinue participation or withdraw their consent at any time. If volunteered by the participant, the reason for discontinuation or withdrawal of consent will be recorded in the CRF. If a patient requests to stop participating, the investigator should ask if the patient would be willing to stop the treatment but continue follow-up. If they do not agree to this, the investigator should ask for their permission to contact them to determine their status on day 28.

### Rescue Criteria

Expected adverse effects of the intervention drug (dexamethasone) include hyperglycemia, hypokalemia, and infection. These adverse effects will be managed according to standard guidelines. If these adverse effects are not successfully treated, the participant will be withdrawn from the study, and the adverse effects will be managed.

### Safety Reporting

#### AE

An AE is any untoward medical occurrence in a participant to whom a medicinal product has been administered, including occurrences that are not necessarily caused by or related to that product. AEs are graded for severity as mild, moderate, severe, and life-threatening as shown in Table 4.

Expected adverse effects of the intervention drug (dexamethasone) are hyperglycemia, hypertension, gastritis, hypokalemia, and infection.

**Table 4. T4:** Common Terminology Criteria for Adverse Events (CTCAE) [25].

Grade	Definition
Grade 1	Mild; asymptomatic or mild symptoms; clinical or diagnostic observations only; intervention not indicated.
Grade 2	Moderate; minimal, local or noninvasive intervention indicated; limiting age-appropriate instrumental ADL^a^^,^^b^.
Grade 3	Severe or medically significant but not immediately life-threatening; hospitalization or prolongation of hospitalization indicated; disabling; limiting self-care ADL^c^.
Grade 4	Life-threatening consequences, urgent intervention indicated
Grade 5	Death related to AE^d^

a ADL: activities of daily living.

b Instrumental ADL refer to preparing meals, shopping for groceries or clothes, using the telephone, managing money, and so on.

c Self-care ADL refer to bathing, dressing and undressing, feeding self, using the toilet, taking medications, and not bedridden.

d AE: adverse event.

#### Serious AE

A serious adverse event (SAE) is any untoward medical occurrence that (1) results in death, (2) is life-threatening, (3) requires inpatient hospitalization or prolongation of existing hospitalization (>21 d), (4) results in persistent or significant disability, or (5) involves any other important medical event that the investigator considers serious (eg, severe hyperglycemia causing diabetic ketoacidosis, gastrointestinal bleeding requiring blood transfusion, and infections causing septic shock requiring inotropic support).

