#### Procedures for Recording AEs

Dexamethasone is an established and commonly used drug with a well-characterized toxicity profile. All AEs (grades 3‐4) will be recorded and reported. Mild and moderate AEs (grades 1‐2) will be recorded only if the investigator considers that the AE is definitely, probably, or possibly related to the study drug. All SAEs will be recorded and reported. If all the information required to report the event is not available initially, the SAE may first be recorded as an initial report, with follow-up and final reports recorded as needed. All AEs, serious and nonserious, will be recorded during the 28-day trial period.

The following information will be recorded: description, onset date and end date, severity, assessment of relatedness to the trial medication, other suspect drug or device, and action taken. Follow-up information should be provided as necessary. All AEs will be followed until resolution or until the event is considered stable.

The investigator will decide whether an AE is sufficiently severe to require the participant’s removal from treatment. A participant may also voluntarily withdraw from treatment because of what he or she perceives as an intolerable AE. If either of these occurs, the participant will undergo an end-of-trial assessment and receive appropriate care under medical supervision until symptoms cease, or the condition becomes stable.

All SAEs will be reported to the IEC within 24 hours of becoming aware of the SAE, and a detailed report will be submitted within 14 days of the event.

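### The unexplained 21-day qualifier on prolonged hospitalization keeps shorter adverse-event-related prolongations out of the SAE definition, and it does not fit the protocol's own reporting deadlines.

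*Protocol article*

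**What the plan says.** All references are to the protocol article.

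- **Serious AE.** An untoward occurrence is serious if it is fatal, life-threatening or disabling, if it "requires inpatient hospitalization or prolongation of existing hospitalization (>21 d" (criterion 3), or if it "involves any other important medical event that the investigator considers serious" (criterion 5). The examples under (5) are ketoacidosis from severe hyperglycemia, gastrointestinal bleeding that needs transfusion, and infection with septic shock on inotropes. Only criterion (3) carries a number of days.
- **AE, Table 4.** Severity grade 3 reads "Severe or medically significant but not immediately life-threatening; hospitalization or prolongation of hospitalization indicated", with no duration.
- **Procedures for Recording AEs.** "All SAEs will be reported to the IEC within 24 hours of becoming aware of the SAE". A detailed report is due 14 days after the event. For other events, "All AEs (grades 3‐4) will be recorded and reported", with no deadline stated. Events of grade 1-2 are recorded only when the investigator judges them at least possibly drug-related. The recording window is fixed: "All AEs, serious and nonserious, will be recorded during the 28-day trial period".
- **Data Safety and Monitoring Board.** The board receives a consolidated summary covering adverse events and SAEs alike.

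**The concern.** Participants are already inpatients when they receive the study drug. For a complication that is neither fatal, life-threatening nor disabling, prolongation of the current stay is therefore the usual route to being classed as serious. Infection is named as an expected effect of dexamethasone under both Rescue Criteria and AE. A day threshold on prolongation closes that route for all but very long stays.

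Two things are at stake. The first is the 24-hour notice to the ethics committee, which only SAEs trigger. The second is a consistent SAE count across three sites: with the clock undefined, two sites can classify the same event differently.

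**Working it through.** The article states no figure to reproduce here. The check is day arithmetic on its own numbers: the 21-day qualifier, the 28-day recording window, the 14-day detailed report and at most 5 days of dosing.

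**1. Added-stay reading.** Count generously, with added stay starting on the day of onset; it cannot start earlier. Stay first exceeds 21 added days on onset day + 22.

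| Onset day | First day above 21 added days | Within 28 days? | Detailed report due (onset + 14) |
|---|---|---|---|
| 1 | 23 | yes | 15 |
| 5 | 27 | yes | 19 |
| 6 | 28 | yes | 20 |
| 7 | 29 | no | 21 |
| 8 | 30 | no | 22 |

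The last onset that can qualify inside the window is day 6. Counting the onset day itself as the first added day would move this to day 7, hence about day 6. In every row seriousness is established 22 − 14 = 8 days after the detailed report was due, if the 14 days run from onset.

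**2. Total-stay reading.** Criterion (3) cannot be met through prolongation before day 22 of the admission. If day 1 is admission, that leaves days 22 to 28, which is 7 of the 28 days. The detailed report for an event on day d is due on day d + 14. It falls before day 22 when d + 14 < 22, that is, for events on days 1 to 7. If dosing starts at admission, this includes every event during the 3 to 5 days of treatment.

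**3. The reading changes the classification.** Two illustrations, with assumed stays:

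- An infection turns a 7-day stay into 14 days. Added stay is 14 − 7 = 7 days and total stay is 14 days. Neither exceeds 21, so criterion (3) is not met on either reading.
- A stay lasts 22 days, of which 7 are due to the infection. Total stay is above 21 and added stay is not. The event meets criterion (3) on one reading and fails it on the other.

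**4. What happens to an event below the threshold.**

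| Route | Does it still apply? |
|---|---|
| Criteria (1), (2), (4): death, life-threatening, disability | Yes, with no day limit |
| Criterion (5): important medical event | Yes, at the investigator's discretion |
| 24-hour ethics committee report | Only if one of the above makes it an SAE |
| Recording as an adverse event | Yes at grade 3-4; at grade 1-2 if judged related |
| Data monitoring board summary | Yes |
| In-hospital complications comparison | Available, whatever the seriousness label |

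**The case against.** The strongest reply is that nothing is lost from the data. Grade 3 in Table 4 covers "hospitalization or prolongation of hospitalization indicated; disabling; limiting self-care ADL" without a day limit, and all grade 3-4 events are recorded. Nosocomial infection and hyperglycemia are watched for in every participant under Data Collection and Management. In-hospital complications are compared between arms as a secondary outcome, and no between-arm SAE comparison is stated. This stands, and it limits the point to classification and expedited reporting.

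Four stronger readings are tempting, and the article does not support them:

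- A reader might infer that the monitoring board does not see these events. It receives all adverse events, not only SAEs.
- A reader might infer that a new admission or readmission must also last more than 21 days. The parenthesis directly follows the words on prolongation, so the natural reading leaves new admissions without a threshold. The wording is loose, but the wider reading is not established.
- A reader might infer that an infection is serious under criterion (5) only with septic shock. The list there is illustrative and the route is open. It does depend on individual judgment, and its infection example suggests a high bar.
- A reader might infer that a patient kept 22 days for the brain injury alone becomes an SAE. The definition first requires an untoward occurrence, so a long stay with no adverse event is not classified at all.

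Three further objections have partial force. Adverse events are followed until they resolve or stabilize, so an event recorded inside 28 days could be upgraded later. That softens the day-6 limit but makes the late classification worse. Severity and seriousness are separate concepts, so the difference from Table 4 is not in itself a contradiction; it shows only that the threshold appears in one place without a reason. Finally, Causality refers to instructions for the AE/SAE data collection tool that are not shown and might define the clock. They would not make a threshold above 21 days fit a 14-day deadline on the added-stay reading.

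**Conclusion.** The point holds as a faulty stated rule that should be fixed; it does not threaten the trial's validity. An adverse event that prolongs the index stay by less than the threshold is not serious under criterion (3). Unless another criterion applies, it gets no 24-hour ethics committee report and does not enter the SAE count.

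The threshold also cannot work with the detailed-report deadline on the added-stay reading. On the total-stay reading it fails for events in the first 7 days of admission. Both statements assume that the 14 days run from event onset. The day-6 limit assumes that added stay is counted from onset, which is the most generous count.

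The number of events affected cannot be estimated, because the article gives neither lengths of stay nor complication rates. The primary endpoint, alpha, power, randomization and adverse event capture are unaffected.

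**What to change.** Delete the 21-day qualifier, so that criterion (3) covers inpatient hospitalization, or prolongation of an existing hospitalization, because of the adverse event. If the aim was to avoid reporting long stays due to the hanging injury, state that as an explicit exemption for stay prolonged by that injury alone, without a new adverse event. Bring Serious AE, Procedures for Recording AEs and the CRF instructions into line, and state when the 14 days start. Check any events in participants already enrolled against the revised definition; the article reports none.

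The cost is a one-line amendment, a CRF instruction update and somewhat more SAE reports. With 3 of 192 participants enrolled at submission, a change now keeps nearly the whole trial under one SAE definition; a later change would mix two. Treatment and the efficacy analysis are not touched.

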#### Causality

The causality of each AE will be assessed by a medically qualified individual to determine its relationship to the trial medication. AEs will be categorized as definite when there is a clear-cut temporal association with the trial study drug. Events will be considered probable when there is a clear temporal association along with improvement after withdrawal of the drug and when the event cannot be reasonably explained by the patient’s known clinical condition or another etiology. Possible AEs will be those with a less clear temporal association, in which other etiologies could also account for the event; such alternative causes will be documented in the CRF. AEs will be classified as not related when there is no temporal association with the trial medication and the event is attributable to other causes, such as concomitant medications, underlying conditions, or the patient’s known clinical condition. The investigator will provide the assessment of causality as per the instructions for completion of the AE or SAE data collection tool.

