**Figure 2. F2:**
[figure not shown]
Medication kit. The left panel shows that a box is labeled with a randomly generated 5-character alphanumeric sequence. The right panel displays the sample medication kit with the same label.

A designated coinvestigator who is the only unblinded person other than the study statistician at the primary site will assume responsibility for crucial aspects of randomization, allocation concealment, and maintenance of the blinding process. All other staff (investigators, nurses, outcome assessors, and research team) and participants remain blinded to treatment assignments throughout the trial. After eligibility confirmation and written consent, the site team contacts the unblinded coinvestigator at the coordinating center. This investigator reconfirms eligibility and consent, performs randomization, and shares only the study drug label number supplied to each site, never revealing the actual treatment allocation.

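### The adverse-event causality scale is out of order: 'definite' asks for less evidence than 'probable', and some events fit no category (minor)

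*Protocol article*

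**What the plan says.** All four definitions stand in one paragraph of the protocol article, under Safety Reporting, Causality.

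- **Definite:** "AEs will be categorized as definite when there is a clear-cut temporal association with the trial study drug". Nothing further is required.
- **Probable:** "Events will be considered probable when there is a clear temporal association along with improvement after withdrawal of the drug", and in addition "when the event cannot be reasonably explained by the patient’s known clinical condition or another etiology".
- **Possible:** "Possible AEs will be those with a less clear temporal association, in which other etiologies could also account for the event". Only here does the paragraph ask for the alternative cause to be written in the case report form.
- **Not related:** "AEs will be classified as not related when there is no temporal association with the trial medication and the event is attributable to other causes". Both conditions must hold.

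On who grades: "The causality of each AE will be assessed by a medically qualified individual to determine its relationship to the trial medication". The paragraph closes by pointing to completion instructions for the event form, which are not shown.

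The grade is used in Procedures for Recording AEs: "Mild and moderate AEs (grades 1‐2) will be recorded only if the investigator considers that the AE is definitely, probably, or possibly related". Grade 3 and 4 events and all SAEs are recorded and reported whatever their relatedness.

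**The concern.** A causality scale should demand more evidence at each step up. Here the top step demands the least. A clearly timed event with an obvious competing cause receives the strongest drug attribution, because 'definite' never asks about other causes and the lower categories cannot take the event.

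The protocol's own text shows that competing causes matter in this population. The Background names aspiration pneumonia and pulmonary complications as problems of near-hanging itself. Study Interventions includes mannitol or hypertonic saline in standard care for both arms. Rescue Criteria and Safety Reporting list infection, hyperglycemia and hypokalemia among the expected effects of dexamethasone. Study drug is given during the first 3 to 5 days.

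Two things are at stake: whether the relatedness grades mean what their names say when an ethics committee, the DSMB or a later reader sees them, and whether every grade 1 or 2 event has a defined category when the recording filter is applied.

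**Working it through.** The plan gives no figure to reproduce. The check is logical and takes its inputs from the four definitions in the Causality section. Three features decide the grade: timing (clear, less clear, none), improvement on withdrawal (yes, no) and an alternative cause (yes, no). That gives 3 × 2 × 2 = 12 combinations. 'Clear-cut' and 'clear' are treated as the same level.

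| Timing | Improves on withdrawal | Alternative cause | Categories met as written |
|---|---|---|---|
| Clear | yes | no | definite and probable |
| Clear | yes | yes | definite |
| Clear | no | no | definite |
| Clear | no | yes | definite |
| Less clear | yes | yes | possible |
| Less clear | no | yes | possible |
| Less clear | yes | no | none |
| Less clear | no | no | none |
| None | yes | yes | not related |
| None | no | yes | not related |
| None | yes | no | none |
| None | no | no | none |

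1. **Inversion.** All 4 clearly timed rows meet 'definite'. One of them also meets 'probable', and no row meets 'probable' without 'definite'. 'Probable' can therefore never be the highest grade that applies.
2. **Forced grade.** For the 2 rows with clear timing and an alternative cause, 'probable' fails on the alternative cause, 'possible' fails because the timing is clear, and 'not related' fails because there is a temporal association. Only 'definite' remains.
3. **Gaps.** Four rows meet no category: less clear or absent timing without an alternative cause.
4. **Count.** 4 (definite) + 2 (possible) + 2 (not related) + 4 (none) = 12.

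**Sensitivity to wording.** Suppose 'clear-cut' was meant to be stronger than 'clear'. An event could then be 'probable' without being 'definite', so the containment in step 1 would no longer be complete. Step 2 would still hold for any event with clear-cut timing, since 'definite' would still ask neither for improvement on withdrawal nor for exclusion of other causes. The gaps in step 3 would remain.

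**Effect on recording.** A grade 1 or 2 event with clear timing and an alternative cause passes the filter now, as 'definite', and would pass after correction, as 'possible'. The inversion alone does not change whether it is recorded. The rows that meet no category are different: the filter needs one of three grades and the text assigns none.

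**The case against.** The strongest reply is that little depends on the label, and most of that reply stands.

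- Analytical Statistics compares in-hospital complications between randomized arms by chi-square or Fisher exact test with relative risk, and applies no relatedness filter. A reader might infer that the trial could not separate dexamethasone effects from the injury. The documents do not support that: randomization against placebo makes the separation, and the comparison does not use the grade.
- All SAEs go to the ethics committee within 24 hours whatever their cause. The DSMB section provides for a summary of all AEs and SAEs, and its Haybittle-Peto rule does not refer to causality.
- On blinding, Randomization and Allocation Concealment says: "All other staff (investigators, nurses, outcome assessors, and research team) and participants remain blinded to treatment assignments throughout the trial". Misgrading should therefore not depend on knowledge of the arm.
- A qualified assessor working from instructions that are not shown may grade more sensibly than the paragraph reads. The record also has a field for another suspect drug or device. That could capture osmotherapy, though not the hanging injury itself.
- Procedures for Recording AEs also says that AEs of every kind are recorded over the 28 days. Read literally, this would close the recording gap. It would also contradict the grade 1 and 2 filter in the same paragraph, so it more naturally sets the time window.

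A second tempting inference is that hanging-related events in general will be graded definitely drug-related. The text forces this only for events whose onset is clearly linked in time to dosing. Less clearly timed events with another cause go to 'possible', and those with no temporal link go to 'not related'. The protocol gives no rate for how many injury-related events would have clear timing.

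The reply does not repair the definitions. This is a rule stated wrongly, not detail left to another document.

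**Conclusion.** The point holds and is minor. As written, the scale is inverted at its top two grades, forces 'definite' on 2 of the 12 combinations despite an evident alternative cause, and leaves 4 of the 12 without a category. These are counts of logical combinations, not event frequencies; the document does not allow a frequency to be estimated.

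The consequence is limited to the relatedness grades in AE and SAE records and reports, and to uncategorised grade 1 and 2 events. No endpoint, test, sample size, SAE reporting trigger or stopping rule is affected.

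The conclusion assumes that the unseen form instructions do not already replace these definitions, that causality is graded by blinded staff, and that the grade 1 and 2 filter is meant to operate as stated. Containment of 'probable' within 'definite' also assumes that 'clear-cut' and 'clear' mean the same.

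**What to change.** Rewrite the four definitions in the Causality section so that they are ordered, mutually exclusive and exhaustive:

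- **Definite:** everything 'probable' requires, plus confirmatory evidence of a kind the trial team names in advance. Nothing here calls for re-exposing a patient.
- **Probable:** the present criteria, where the evidence for 'definite' is lacking.
- **Possible:** any event with a plausible temporal association that does not meet 'probable'. State that this includes clear timing with an alternative cause, clear timing where withdrawal is uninformative (drug continued, event treated, or event fatal), and less clear timing with no alternative cause.
- **Not related:** the remainder.

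Taking clear and less clear timing as plausible, the 12 combinations then divide into 1 for 'definite' or 'probable' (split by the confirmatory evidence), 7 for 'possible' (3 clear, 4 less clear) and 4 for 'not related': 1 + 7 + 4 = 12, with no overlap and no gap. The wide 'possible' category matters. If 'definite' were tightened without widening 'possible', a clearly timed event with no other cause and no informative withdrawal would lose the category it now has.

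Align the AE and SAE form instructions, and ask for any alternative cause to be recorded for every graded event. The between-arm comparison of complications needs no change.

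The cost is one paragraph and one form instruction. At manuscript submission 3 patients were enrolled and two of the three sites had not started, so re-grading should be slight.
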